## Abstract

**Introduction:**

About 17–80% stroke survivors experience the deficit of upper limb function, which strongly influences their independence and quality of life. Robot-assisted training and functional electrical stimulation are commonly used interventions in the rehabilitation of hemiplegia upper extremities, while the effect of their combination remains unclear. The aim of this trial is to explore the effect of robot-assisted upper limb training combined with functional electrical stimulation, in terms of neuromuscular rehabilitation, compared with robot-assisted upper limb training alone.

**Methods:**

Individuals (*n* = 60) with the first onset of stroke (more than 1 week and less than 1 year after stroke onset) will be considered in the recruitment of this single-blinded, three-arm randomized controlled trial. Participants will be allocated into three groups (robot-assisted training combined with functional electrical stimulation group, robot-assisted training group, and conventional rehabilitation therapies group) with a ratio of 1:1:1. All interventions will be executed for 45 min per session, one session per day, 5 sessions per week for 6 weeks. The neuromuscular function of the upper limb (Fugl-Meyer Assessment of upper extremity), ability of daily life (modified Barthel Index), pain (visual analogue scale), and quality of life (EQ-5D-5L) will be assessed at the baseline, at the end of this trial and after 3 months follow-up. Two-way repeated measures analysis of variance will be used to compare the outcomes if the data are normally distributed. Simple effects tests will be used for the further exploration of interaction effects by time and group. Scheirer-Ray-Hare test will be used if the data are not satisfied with normal distribution.

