#### Inclusion criteria

Aged 18 to 80Clinical diagnosis of stroke (cerebral infarction, primary intracerebral haemorrhage, subarachnoid haemorrhage, etc.)Between 1 week and 1 year since the first onset of strokeUpper limb, functional limitation: the score of Fugl-Meyer Assessment of Upper Extremity (FMA-UE) ≥ 11 and ≤ 33All of the following muscle strengths assessed by manual muscle test (shoulder flexion/extension, shoulder abduction/adduction, elbow extension/flexion, wrist flexion/extension) ≤ 3Sufficient to offer consent to take part in this study and able to follow the requirements of the protocol

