### Sample size

The sample size is 60 subjects (20 subjects in each group). As we did not retrieve an appropriate study, according to Cohen’s theory [17], the effect size of 0.25 was applied. G*Power was used to estimate the sample size (repeated measures analysis of variance (ANOVA), within-between interaction) with effect size = 0.25, *α* = 0.05, 1 − β = 0.95, and the number of groups = 3. The total sample size based on the result was 54 (18 subjects per group). Considering 10% attrition, we inflated the total sample size to 60.

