## Statistical methods

Normally distributed variables will be presented by means with standard deviations, and nonnormally distributed data will be presented by medians with interquartile ranges. Categorical variables will be presented by proportion and frequency.

Investigators in charge of the result analysis will be blinded to the group allocation. All data will be analysed by Statistical Package for the Social Science (SPSS) version 26.0 software. The score of the primary outcome and secondary outcomes will be measured at different time points for the same subject. Two-factor repeated-measures analysis of variance (ANOVA) will be used for the statistical analysis for all outcomes with the sphericity test before analysis. If the data is dissatisfied with the sphericity test, the Green-house-Geisser method will be used to correct it. Simple effects tests will be used for the further exploration of interaction effects by time and group. Scheirer-Ray-Hare test will be used if the data are not satisfied with normal distribution. The statistical difference will be set at a *P* value less than 0.05.

The subgroup analysis will be conducted for further exploration. The comparison will be conducted between people with the first stroke onset for less than three months and residual people in terms of the score of FMA-UE. We will test whether RTFE shows the same effectiveness in people with different durations after first stroke onset by two-factor repeated measures ANOVA with the same statistical difference.

All analyses in this trial will follow the intention-to-treat principle. Based on this principle, all participants no matter what kind of intervention they received will be regarded as randomized. Multiple imputations based on 5 replications and the Markov-chain Monte Carlo method in the SAS MI procedure will be used to handle the missing data.

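### An undefined normality check decides whether the repeated-measures ANOVA that sized the trial is used, and failing it switches to a test that ignores the pairing of visits

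*Protocol article*

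**What the plan says.** Statistical methods in the protocol article names a default: "Two-factor repeated-measures analysis of variance (ANOVA) will be used for the statistical analysis for all outcomes with the sphericity test before analysis". Further down the same paragraph comes the exception: "Scheirer-Ray-Hare test will be used if the data are not satisfied with normal distribution". The abstract puts the same rule the other way round: "Two-way repeated measures analysis of variance will be used to compare the outcomes if the data are normally distributed".

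The Sample size section rests on the default method only, described as "repeated measures analysis of variance (ANOVA), within-between interaction", with an effect size of 0.25, "1 − β = 0.95, and the number of groups = 3". It arrives at 54 patients, raised to 60 for attrition.

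Three other places bear on the point. Study design sets three assessments (baseline, 6 weeks, 3 months). Inclusion criteria restrict FMA-UE at entry to 11-33. Primary outcome names FMA-UE at week 6 and gives a minimal clinically important difference of 12.4 points for the upper extremity.

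**The concern.** The main analysis is chosen by looking at outcome data, and the rule for choosing is open. The trigger refers only to the data. That could mean the week-6 score, each visit, each of the nine arm-by-visit cells, all 180 values together, or the model residuals. These readings fail a normality test at very different rates, and the article does not choose between them.

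Two features of the trial make failure more likely on some readings. The entry range cuts off both tails of baseline FMA-UE. Recovery over three visits, plus any treatment effect, makes pooled values a mixture of distributions.

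Three things are at stake:

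- The power calculation describes a test that may not be the one reported.
- The replacement ranks all observations as if independent, so it does not remove between-patient variation from the error term. That removal is what makes a repeated-measures design efficient.
- A result on ranks gives no difference in FMA-UE points to set against 12.4.

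**Working it through.** **1. The plan's own figure.** Inputs from Sample size: f = 0.25, α = 0.05, power 0.95, 3 groups. Three measurements are taken from Study design. Correlation 0.5 and sphericity (ε = 1) are not stated and are assumed.

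- λ = f² × N × m / (1 − ρ) = 0.0625 × 54 × 3 / 0.5 = 20.25
- df = (3 − 1)(3 − 1) = 4 and (54 − 3)(3 − 1) = 102
- Power = 0.958, so 54 is reproduced
- 54 / 0.9 = 60, and power with all 60 is 0.975

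The stated size therefore belongs to the ANOVA interaction test.

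**2. The fallback at that same effect.** With 18 per arm, f = 0.25 and normal data, interaction power is:

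| Correlation | ANOVA | Scheirer-Ray-Hare | Scheirer-Ray-Hare with about 1 SD change over time |
|---|---|---|---|
| 0.5 | 0.96 | 0.45 | 0.12 |
| 0.7 | 0.998 | 0.39 | 0.07 |

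The fallback's type I error is 0.0005 or below, against a nominal 0.05. Variation between patients and over time inflates its denominator.

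**3. How often the switch occurs.** Assumptions: 20 per arm; Shapiro-Wilk at 0.05; baseline N(22, 6) or uniform on 11-33; week 6 = baseline + 10 + N(0, 6); 3 months = week 6 + 3 + N(0, 4).

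| Values checked | Normal data | Flat 11-33 baseline |
|---|---|---|
| Week-6 score only | about 5% | about 4% |
| Each of 3 visits | 11-13% | about 90% |
| Nine arm-by-visit cells | 35% | about 60% |
| All 180 values pooled | 43% with no effect, 54-55% with a 6-point effect | 66-68% with no effect |

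The nine-cell rate with normal data is close to what nine independent tests give by chance: 1 − 0.95⁹ = 0.37.

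**4. What the switch costs.** With no switch, the ANOVA's type I error is 4-6% with normal data, with a flat baseline and with skewed (gamma) gains. Its power for a 6-point effect of the combined therapy at both follow-ups is 82-86%. Under these assumptions the fallback's interaction power is about 0%, so two-stage power is approximately (1 − switch rate) × ANOVA power. Taking 86%:

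- Week 6 only: 0.95 × 0.86 = 82%
- By visit, normal data: 0.88 × 0.86 = 76%
- Nine cells, normal data: 0.65 × 0.86 = 56%
- Pooled, normal data: 0.45 × 0.86 = 39%
- By visit, flat baseline: 0.10 × 0.86 = 9%

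This agrees with the simulated range of 8-76% for the two-stage rule on the readings that go beyond the week-6 score. The first line shows that a check confined to week 6 costs little when gains are normal.

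**The case against.** A reader might infer that the protocol tests raw values where it should test residuals, and that a perfectly valid ANOVA is therefore dropped in a third to nine tenths of trials. The documents do not support this, for three reasons.

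- The article says only the data. It names no test, level or set of values, and the phrase is common shorthand in a condensed report. Raw-value testing is one literal reading, not a stated rule.
- The raw-versus-residual contrast explains little. Within a cell, a residual is the raw value minus a constant, so the nine-cell rate is the same for both; it comes from multiple testing. With a flat baseline, residuals checked by visit also fail about 70% of the time. That ANOVA cannot be called perfectly valid by a residual-normality standard, although it keeps its error rate. Only pooling all values separates the two clearly (normal data: raw about 44%, residuals 14-24%).
- A range starting at a third leaves out readings that are just as literal and give about 4-13%.

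Other points on the plan's side carry some weight. The switch is specified in advance and the analysts are blinded to allocation, which limits selective choice. Medians and interquartile ranges would still describe scores in points, though not as a treatment effect. The power loss comes from this particular fallback; a rank method that respected the repeated measures would lose less. An unseen analysis plan may define the check. That would settle the switch rate, but not the choice of a replacement that ignores pairing, which the article fixes.

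**Conclusion.** The concern holds in a limited form. The article makes its main analysis conditional on an unspecified normality check, and failing that check replaces the method that sized the trial with one that has far less power for the interaction. The switch rate is not a single property of the plan: it runs from about 4-5% to about 90%, depending on what is checked and on the shape of the baseline. The cost per switch is large on every reading, because the ANOVA did not need replacing in any scenario examined.

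The simulated rates and the 6-point power figures depend on assumed means, SDs, recovery and Shapiro-Wilk at 0.05, none of which the protocol gives. The comparison at f = 0.25 uses the protocol's own effect size but an assumed correlation. Only FMA-UE was examined, so nothing is shown here about the error rate of ANOVA for VAS or EQ-5D-5L.

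**What to change.** In the abstract and in Statistical methods:

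- Delete the normality condition.
- Name the parametric repeated-measures model as the primary analysis of FMA-UE, whatever a normality check shows.
- Use residual plots as a diagnostic only. Testing residuals as a gate is no cure: cell by cell it would fail as often as the raw values do.
- Move the rank-based analysis to a sensitivity analysis, and replace Scheirer-Ray-Hare with a rank or permutation method that keeps each patient's three visits together.
- For the bounded secondary outcomes (VAS, EQ-5D-5L), also fix one method in advance and do not let a normality test choose it.

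The cost is a change to two sentences and one extra sensitivity analysis per outcome. The sample size calculation would then refer to the test actually reported.

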**Discussion:**

We expect this three-arm randomized controlled trial to explore the effectiveness of robot-assisted training combined with functional electrical stimulation in improving post-stroke upper limb function compared with robot-assisted training alone.

**Trial registration:**

Effect of upper limb robot on improving upper limb function after stroke, identifier: ChiCTR2300073279. Registered on 5 July 2023.

## Introduction

Stroke is one of the leading causes of death and disability around the world, which causes huge pressure on the global health system [1, 2]. Seventeen per cent to 80% of stroke survivors experienced the impairment of motor function of the upper limb, which significantly obstacles their independence and self-caring [3–5].

Conventional rehabilitation therapies (CRTs), mainly including task-oriented activities, activities of daily living (ADL) practice, instrumental activities of daily living (IADL) practice and constrain-induced movement therapy, is a widely-used and high-efficiency intervention in the recovery of upper limb function, which has been recommended in recent American Heart Association guidelines in class I [6]. However, its high human cost and time consumption always restrict patients to access to sufficient therapy [7].

An alternative approach is upper limb robot-assisted therapy (RT) as it can provide high-intensity and cost-effective training to reduce the pressure on human cost. One recent big-sample multicenter randomized controlled trial (RCT) and several systematic reviews reveal that RT is equivalent to CRTs in developing post-stroke upper limb neuromuscular function [8–10]. However, passive movement offered by robots does not provide sufficient activation and stimulation to hemiplegic muscles.

For further improving effectiveness, RT is combined with other therapeutic techniques like functional electrical stimulation (FES) [11, 12]. FES is a kind of neuromuscular electrical stimulation (NMES) generating muscle contraction during tasks or activities [13]. FES forces target muscle group contracting to improve the participation of patients and intensify the force and sensory feedback, which compensates for the disadvantage of RT. On the other hand, FES therapy requires patients to perform specific tasks during electrical stimulating, which is a huge challenge for stroke survivors. Supportive movement provided by robot promotes the completion of tasks. Considering this intrinsic complementary mechanism, Robot-assisted training combined with functional electrical stimulation (RTFE) seems a promising intervention in stroke function reconstruction. Nevertheless, scarce studies focus on the effectiveness of RTFE on post-stroke upper limb neuromuscular function. Existing RTFE studies mainly concentrate on developing FES controllers from an engineering perspective [14–16]. Most of them are small sample size and lack of comparison [14–16]. Katie’s research showed RTFE improve the motor function of the forearm; however, this trial, without the control group, only recruited 5 subjects [15]. Similarly, one trial investigated RTFE’s effect in stroke survivors but just on hand function with 5 subjects. Furthermore, these new-type RTFE system with advanced controllers seems not to be applied in clinical situations in a short time as they are mainly in the laboratory stage.

There is an urgency to conduct a clinical study to investigate the rehabilitative effectiveness of RTFE. The aim of this trial is to explore the effectiveness of RTFE on developing post-stroke upper limb neuromuscular function.

## Objective and hypothesis

The primary objective of this study is to investigate the effectiveness of RTFE on the upper extremity neuromuscular function in stroke patients. The null hypothesis is that there is no difference among participants who receive RTFE, RT and CRTs in terms of upper limb neuromuscular function development. The secondary objective is to investigate whether RTFE is superior to RT with respect to improving the ability of ADL, quality of life and reducing post-stroke pain.

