## Outcomes

### Primary outcome

#### FMA-UE (Fugl-Meyer Assessment of Upper Extremity)

The primary outcome of this study is the upper limb neuromuscular function measured by FMA-UE at the end of week 6. FMA-UE is an assessment of the upper extremity in terms of neuromuscular function with high intra- and inter-reliability and concurrent validity [19, 20]. This scale consists of 33 items, which mainly focus on the reflex activity, volitional movement and functional movement of the upper extremity, wrist and hand, with the score of each item ranging from 0 to 2 (0 = no performance at all; 1 = partial performance; 2 = full performance). The maximum score for this assessment is 66 and the minimal clinically important differences are 12.4 (upper extremity), 5.6 (upper arm), and 4.9 (wrist/hand) [21]. A higher FMA-UE score means better performance in neuromuscular function.

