## Discussion

We suppose that this trial will reveal the effectiveness of RTFE on upper limb dysfunction after stroke. One experiment conducted by Meadmore investigated the FES mediated by iterative learning control plus robotics in reducing motor impairment in 5 chronic stroke patients [15]. A significant improvement was observed after 18 RT sessions in subjects. Our RCT will provide evidence of comparison among three groups and further explore the reliability of this conclusion with a bigger sample size. Although FES in our study is based on the open-loop design, considering this is the most widely used FES and most FES with new-type controllers are still immature, this might be the easiest protocol to implement, which makes the result of our trial with high practical value. Straudi’s recent study investigated robot-assisted hand training with FES in improving the hand function of stroke patients [11]. The result shows an equivalent improvement between the RTFE group and the CRT group. Our trial focuses on the proximal joints of the upper limb, and the result of this trial will reveal the influence of RTFE on shoulder, elbow, and wrist neuromuscular function after stroke.

There are several strengths and weaknesses of this trial. Firstly, compared with previous self-controlled study, this study is a well-structured 3-arm RCT. Our study compares the effect between RTFE with RT alone to explore the overlapping effect of this combination therapy. Then, this study adopts various methods to reduce the bias and enhance the reliability as possible. Considering the difference of neuroplasticity potential in stroke survivors at different stages, stratification by baseline of time after the first-ever stroke is used to reduce the heterogeneity among the three groups. The use of a randomized block design reduces the bias and promotes balance in the allocation. The systematic imputation strategies further guarantee data and conclusion’s reliability. Additionally, the use of intention-to-treat analysis reduces the selection bias. Although not all interveners and participants are blinded, the blinding still covers assessors, RT therapists, CRT therapists and participants in the RT and RTFE groups for reducing potential bias.

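### The trial asks whether RTFE beats RT alone, but the FMA-UE null and the sample size concern a three-arm omnibus test that can be rejected with no FES effect

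*Protocol article*

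**What the plan says.** The article frames the question as RTFE versus RT in three places. The abstract's introduction gives the aim as the effect of the combination "compared with robot-assisted upper limb training alone". The abstract's discussion expects the trial to show effectiveness "in improving post-stroke upper limb function compared with robot-assisted training alone". The main Discussion states "Our study compares the effect between RTFE with RT alone".

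The formal text differs. Under Objective and hypothesis, the primary objective names no comparator, and the null is "no difference among participants who receive RTFE, RT and CRTs in terms of upper limb neuromuscular function development". Superiority of RTFE over RT is written only into the secondary objective: "whether RTFE is superior to RT with respect to improving the ability of ADL, quality of life and reducing post-stroke pain".

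The Sample size section uses the within-between interaction of a repeated-measures ANOVA with effect size 0.25, alpha 0.05, power 0.95 "and the number of groups = 3". It arrives at 54, raised to 60 for 10% attrition. Statistical methods specifies a two-factor repeated-measures ANOVA and adds: "Simple effects tests will be used for the further exploration of interaction effects by time and group".

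Under Interventions, all arms receive the same 45-minute daily CRT session. RT adds 45 minutes of robot training with sham stimulation, and RTFE adds the same robot training with active stimulation. Primary outcome fixes FMA-UE at the end of week 6.

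**The concern.** Only RTFE versus RT isolates the stimulation, since those two arms share the same CRTs and the same robot training and differ in active or sham FES. Against CRTs, both robot arms differ by an extra session, 90 against 45 scheduled minutes a day. The add-on design is sound and openly described. Its consequence is that the three-arm null is false whenever the extra session helps, whether or not FES contributes. A significant primary test would then be correct for the null as written and would still leave the trial's question unanswered.

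The contrast that does answer it has no confirmatory status for FMA-UE, and the 95% power in the protocol does not apply to it. This sits oddly with the secondary outcomes, for which that same contrast is a stated hypothesis.

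**Working it through.** **Inputs.** From the protocol: f = 0.25, alpha 0.05, power 0.95, k = 3 groups, 54 before and 60 after 10% attrition (Sample size); three assessments (Study design); a minimal clinically important difference of 12.4 points on FMA-UE (Primary outcome). The protocol gives no FMA-UE SD, no correlation between visits and no effect of the added session, so these are assumed and varied.

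**1. The plan's own figure.** For the within-between interaction with m = 3 measurements, correlation ρ = 0.5 and sphericity assumed, λ = f²·N·m/(1 − ρ) = 0.0625 × 54 × 3/0.5 = 20.25, with (k − 1)(m − 1) = 4 and (N − k)(m − 1) = 102 degrees of freedom. Power is 0.958 at N = 54 and 0.946 at N = 51, so 54 reproduces, and 54/0.9 = 60. The arithmetic is not in dispute.

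**2. What that 95% power can be spent on.** Let RTFE = RT = δ SD above CRT at week 6 and 3 months, with no difference at baseline. The variance of the group pattern (1, 1, 0) is 2/9, and that of the time pattern (0, 1, 1) is 2/9, so f = √(2/9 × 2/9)·δ = (2/9)δ. Setting f = 0.25 gives δ = 1.125 SD. In 20,000 simulated trials (ρ = 0.5):

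| Pattern at f = 0.25 | RTFE − RT at week 6 | Omnibus rejects, 18 / 20 per arm | RTFE vs RT rejects, 18 / 20 per arm |
|---|---|---|---|
| RTFE = RT > CRT | 0 | 95.8% / 97.5% | 4.9% / 4.9% |
| Graded, RT halfway | 0.65 SD | 95.7% / 97.5% | 47% / 51% |
| RTFE > RT = CRT | 1.125 SD | 95.7% / 97.5% | 90% / 93% |

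RTFE versus RT is tested here on change from baseline to week 6. The omnibus power is the same in every row, while the power for the FES question runs from 5% to about 90%.

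**3. Smaller effects of the added session, FES effect zero.** Simulated rejection rates of the group-by-time test:

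| δ (assumed) | 20 per arm, ρ 0.5 | 20 per arm, ρ 0.7 | 18 per arm, ρ 0.5 | 18 per arm, ρ 0.7 |
|---|---|---|---|---|
| 0.3 | 0.139 | 0.210 | 0.126 | 0.191 |
| 0.5 | 0.341 | 0.540 | 0.315 | 0.501 |
| 0.8 | 0.757 | 0.946 | 0.705 | 0.915 |

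The noncentral F agrees within about one point. For example, at δ = 0.5, 20 per arm and ρ = 0.5, f = 0.111, λ = 0.01235 × 60 × 3/0.5 = 4.44, and power is 0.34. The baseline-adjusted RTFE–RT test at week 6 in the same trials rejects in 0.048 to 0.052.

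**4. Power of RTFE versus RT at week 6.** Two-sided 0.05, noncentral t. With baseline adjustment the residual SD is √(1 − r²), on 2n − 3 degrees of freedom.

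| | 18 per arm | 20 per arm |
|---|---|---|
| Detectable at 80%, unadjusted | 0.96 SD | 0.91 SD |
| Adjusted, r = 0.5 | 0.83 SD | 0.79 SD |
| Adjusted, r = 0.7 | 0.69 SD | 0.65 SD |

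Against 12.4 points, unadjusted:

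| Assumed SD | 8 | 10 | 12 | 15 |
|---|---|---|---|---|
| 18 per arm | 99.5% | 95% | 85% | 67% |
| 20 per arm | 99.8% | 97% | 89% | 72% |

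Power reaches 80% at 18 per arm only if the SD is at most 12.4/0.961 = 12.9 unadjusted, or 14.9 or 18.1 with adjustment at r = 0.5 or 0.7.

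**The case against.** The RTFE-versus-RT wording comes from the abstract and Discussion. The aim at the end of the Introduction and the primary objective speak only of the effectiveness of RTFE, and the Discussion also promises a comparison among the three groups. The null, sizing and analysis agree with one another. An omnibus test followed by simple effects is a conventional three-arm plan that can reach this pair, and a full protocol or SAP may name the contrast. All of that is fair as description. But the follow-up tests are labelled exploratory, and the null and the sized test are fixed in this document, so the mismatch is in what is stated and not in omitted detail. An omnibus that the added session alone can drive does not establish the effectiveness of RTFE either.

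The Introduction cites RT as equivalent to CRTs, which would favour the pattern where only RTFE differs. Here, however, RT is added to CRTs, so RT exceeding CRTs is plausible.

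On size, the objection has more force. The entry range of 11 to 33 on FMA-UE caps the entry SD at half of 22, or 11, and a uniform spread would give about 6.4. Scores may widen by week 6, but power for 12.4 points could well be good. Nor should one lean on the comparison at fixed f, where a two-group interaction has 91% power at 18 per arm: f = 0.25 means 1.06 SD in two groups but 1.125 SD in three, and at 1.125 SD the two-group figure is 93.7%. The error rate of the pair is not inflated. These points limit the consequence without removing the mismatch.

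**Conclusion.** The concern holds as a fault in which question the primary test answers. It is not an error in the arithmetic of 54 and 60, and it does not show that the trial is underpowered. At the planned effect size the omnibus test can have its full 95.8% power with no FES effect. With assumed added-session effects of 0.3 to 0.8 SD it rejects in 14% to 95% of trials at 20 per arm. These rates rest on assumed correlations of 0.5 or 0.7 and equal correlation across visits. Whether RTFE versus RT is adequately powered depends on the week-6 FMA-UE SD and the baseline correlation, neither of which the protocol gives. It should be corrected, because it changes what a positive result would mean.

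**What to change.** In Objective and hypothesis, name RTFE versus RT on FMA-UE at week 6, adjusted for baseline, as the primary contrast. The mismatch is cured by naming the contrast; the adjustment is recommended because it lowers the detectable difference at no cost.

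In Sample size, add the detectable difference for that contrast at 80% power and two-sided 0.05: 0.96 SD at 18 per arm and 0.91 SD at 20 unadjusted, and about 0.83 or 0.69 SD at 18 per arm with adjustment at assumed correlations of 0.5 or 0.7. State the FMA-UE SD assumed, and note that 12.4 points has at least 80% unadjusted power at 18 per arm only if the SD is about 12.9 or less.

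Make RT versus CRT and RTFE versus CRT secondary, and interpret them as CRTs plus an added session against CRTs alone.

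The change needs no further data collection and, at the planned size, no further patients; Trial status reports that none had been recruited. The price is a less favourable power statement and a narrower claim from the CRT arm. If the sponsor wants to detect a smaller FES effect, the size itself would need revisiting: 0.5 SD unadjusted takes 64 per arm for 80% power.
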